## **Sub-trial: Pharmacokinetics**

### **Aim**

We wish to investigate the plasma concentrations of fosfomycin and metronidazole after intraperitoneal administration in patients diagnosed with uncomplicated appendicitis.

### **Primary outcome**

The plasma concentrations of fosfomycin over time are measured with high-performance liquid chromatography mass spectrometry (HPLC-MS).

**Secondary outcomes**

The plasma concentrations of metronidazole over time are measured with HPLC-MS and microbiological investigations of specimens from appendices and/or abdominal fluid removed during surgery.

**Design**

An open-label, phase II, pharmacokinetic pilot study of 8 participants.

**Trial participants**

The inclusion and exclusion criteria are similar to the criteria of the main trial: Safety and are seen in the section Trial participants.

**Trial course**

The trial course is outlined in Figure 2. We expect that eight of the participants from the main trial on safety also will participate in this sub-trial on pharmacokinetics. The trial course is similar to the course described for the main trial: Safety with the addition of the following. If excess fluid is discovered in the abdomen at the beginning of the surgery, this will be collected for microbiological investigations. When the appendix has been removed from the abdominal cavity through an Endobag, a swab from the appendix will be collected for microbiological investigations before it is sent for pathological evaluation. A baseline blood sample is collected from a large peripheral vein during the surgery immediately before the trial treatment is given. Blood samples will be collected at ½, 1, 2, 4, 8, 12, and 24 hours after the trial treatment from large peripheral veins or through an intravenous access. The blood sample at ½, 1, and 2 hours will be collected with a leeway of ±15 minutes. The blood sample at 4, 8, and 12 hours will be collected with a leeway of ±30 minutes. The blood sample at 24 hours after surgery will be collected with a leeway of ±4 hours. The collection of blood samples will be noted in the CRF.

[figure not shown]

Figure 2. The trial course for participants in the sub trial: Pharmacokinetics. An outline (black text) of the normal course of admission for appendicitis is seen at the bottom. The timespan for enrolment and inclusion are marked in grey boxes. All investigations related to the trial are shown in blue text and in the blue boxes. These include repeated blood samples and a swab from the removed appendix and/or excess fluid in the abdominal cavity.

## Measurements

### Primary outcome:

- Plasma concentrations of fosfomycin over time measured by HPLC-MS will be analysed at Faculty for Pharmacy, University of Copenhagen. 4 ml of blood will be collected per sample. A research biobank will be established for the collected samples, which will be frozen and stored at -80°C for one year. Thereafter the plasma samples are destroyed. However, the analysed samples without plasma (and thereby without human residues) are stored until the study has been published.

### Secondary outcomes:

- Plasma concentrations of metronidazole over time measured by HPLC-MS will be analysed at Faculty for Pharmacy, University of Copenhagen. 4 ml of blood will be collected per sample. A research biobank will be established for the collected samples, which will be frozen and stored at -80°C for one year. Thereafter the plasma samples are destroyed. However, the analysed samples without plasma (and hence without human residues) are stored until the study has been published.
- Microbiological flora and susceptibility: The specimens collected during the surgery from the abdominal excess fluid and/or swab from the appendices are immediately sent to the Department of Clinical Microbiology, Herlev Hospital, where they are investigated. Hereafter, the collected human material is destroyed. However, the cultured bacteria (without human residues) will be frozen at -80°C and stored for 3 years.

## Statistics

The number of patients needed for the trial is not based on a power calculation. This trial is a pilot study of the pharmacokinetics of intraperitoneal administration of fosfomycin and metronidazole. We have decided that 8 patients are needed to collect a minimum of information of how the plasma concentrations develop over time.

The continuous numerical data will be reported as mean and standard deviation if normally distributed. If not normally distributed, continuous numerical data will be reported as median and percentiles. Data from HPLC-MS analysis will be used to calculate e.g. the area under the curve (AUC), the maximum concentration observed ( $C_{\max}$ ), the time point for the maximal concentration ( $T_{\max}$ ), and the terminal phase half-life ( $T_{1/2}$ ).

## Withdrawal and dropout criteria

The participants can withdraw their consent at any point during the trial. If the participant becomes unstable during the surgery, the primary investigator can exclude the participant from the trial for the safety of the participant. This will be effectuated in case of:

- Severe intra-abdominal bleeding
- Allergic reaction to general anaesthesia
- Other severe complications during surgery

A participant has concluded the sub-trial after the last blood sample has been collected 24 hours  $\pm$  4 hours after the trial treatment.

## Other drugs during the trial

The patients can receive any analgesic medication necessary before or after the surgery. Further, patients can receive intravenous fluids without restrictions. The medication necessary for anaesthesia, thrombosis prophylaxis, and the treatment of nausea can be administered without restrictions. These will be noted in the CRF.

## Side effects

In the following sections the side effects of each drug is described. The side effects of fosfomycin and metronidazole are based on the literature and their respective summary of product characteristics. The summary of product characteristics for fosfomycin and metronidazole will be the reference document for side effects and adverse events. The side effects of GM-CSF are based on the available literature. The reference document for side effects and adverse events of GM-CSF will be the Investigators Brochure. The most common side effects are listed in Table 1 and are experienced by 1-10% of patients receiving the drugs.

| Type of side effect     | Fosfomycin               | Metronidazole  | GM-CSF                  |
|-------------------------|--------------------------|----------------|-------------------------|
| Gastrointestinal | Abdominal pain           | Dry mouth      | Diarrhoea               |
|                         | Vomiting                 | Metal taste    | Nausea                  |
|                         |                          | Nausea         | Vomiting                |
|                         |                          | Oral mucositis |                         |
|                         |                          | Stomatitis     |                         |
| Skin             | Injection site phlebitis |                | Injection site reaction |
|                         |                          |                | Rash                    |
| Other            |                          |                | Anorexia                |
|                         |                          |                | Asthenia                |
|                         |                          |                | Dyspnoea                |
|                         |                          |                | Fatigue                 |
|                         |                          |                | Fever                   |
|                         |                          |                | Musculoskeletal pain    |
|                         |                          |                | Rigors                  |

Table 1. The most common side effect of fosfomycin, metronidazole, and granulocyte-macrophage colony-stimulating factor (GM-CSF).

### Side effects of fosfomycin

Fosfomycin is generally well tolerated. A surveillance study of more than 35,000 patients receiving orally administered fosfomycin reported side effects in less than 3.5% of the patients. The most common side effects were gastrointestinal disturbances such as vomiting and abdominal pain, which are common side effects of many antimicrobial agents. Further, after intravenous administration of doses of 4 g fosfomycin 4 times a day in 11 critically ill patients, no adverse events was experienced. Diarrhoea was reported in one child after intravenous doses of 200 mg/kg fosfomycin were administered in 23 children suffering from osteomyelitis. Other studies reported high sodium, which is the dose limiting factor, and more seldom: allergic reactions, headache, rhinitis, vaginitis, and

phlebitis. In pharmacokinetic studies where fosfomycin was administered intraperitoneally adverse events were not reported.

### **Side effects of metronidazole**

Metronidazole is routinely administered intravenously to treat peritonitis e.g. after perforation of the appendix. It is generally well tolerated. The known side effects of intravenous administration include metal taste, nausea, oral mucositis, stomatitis, and dry mouth. Some patients who consume alcohol together with metronidazole experience a disulfiram-like (Antabuse-like) reaction. Further, the urine can be coloured deeply red.

Two studies reported no adverse reactions after a single abdominal installation of metronidazole (500 mg in 100 ml fluid) in the peritoneum and wound during closure after open surgery for complicated appendicitis or laparotomy.

### **Side effect of the combination of fosfomycin and metronidazole**

The combination of fosfomycin and metronidazole has been administered intravenously in patients undergoing either elective or emergency colorectal surgery. Only few side effects were reported in these studies and included: gastrointestinal side effects such as nausea and vomiting and skin reactions (urticaria, thrombophlebitis, purpura, and skin rash).

### **Side effects of GM-CSF**

GM-CSF has overall been reported well tolerated regardless of route of administration. GM-CSF administered intravenously in an RCT in patients requiring admission to the intensive care unit reported reversible oliguria as the only side effect. A pharmacokinetic study of escalating doses (0.3, 1, 3, 10, 15, and 20 µg/kg/day) in patients with advanced malignancy and/or neutropenia reported the following most common adverse clinical effects: 71% bone pain, 62% lethargy/malaise, 38% rash and/or pruritus, 38% first dose reaction, 29% fever, 24% fever and rigors, 14% weight dose gain, 10% marginal keratitis, 10% nasal congestion, and 10% pericardial pain. Adverse effects such as fever, pericarditis, and liver abnormalities were not seen in

patients receiving  $<10 \mu\text{g/kg}$ . Also transient leukopenia was seen after intravenous administration. The first dose reaction is characterised by either symptomatic hypotension, hypoxia or both and at least two other common symptoms (flushing sensation, muscular or bone aches, throbbing lumbar back pain, dyspnoea, nausea and vomiting, rigor or fever, and involuntary leg spasms). This happened within  $60 \pm 40$  minutes after intravenous injection or infusion. Subcutaneous administration in patients with sepsis resulted in no side effects. However, the first dose reaction was associated with high serum concentrations and an intravenous administration route. Another pharmacokinetic study reported bone pain, chills/rigors, dyspnoea, fever, serositis and thrombosis after intravenous administration of escalating doses of GM-CSF of 1, 2, 4, or  $8 \mu\text{g/kg/day}$ . One pharmacokinetic study did not report on adverse effects.

An RCT reported the following adverse reactions after a dose of  $3 \mu\text{g/kg/day}$  GM-CSF administered subcutaneously to patients with abdominal sepsis: thrombocytopenia, generalised rash, nausea, deep vein thrombosis, and superficial phlebitis. A pharmacokinetic dose escalating study reported the following adverse effects: fever, bone pain, arthralgia/myalgia, skin reaction, increased liver enzymes, thrombocytopenia and pericarditis after subcutaneously administered doses of 0.3, 1, 3, 10, 15, 20, or  $30 \mu\text{g/kg/day}$  to patients with advanced malignancy. Pericarditis occurred only after high doses. The transient leukopenia seen after intravenous administration arose later after subcutaneous administration. One pharmacokinetic study did not report on adverse effects.

Only a transitory flu-like syndrome was reported after doses of  $68 \mu\text{g/day}$  GM-CSF administered intraperitoneally in patients undergoing peritoneal dialysis. A pharmacokinetic study reported fever and serositis after intraperitoneal administration of escalating doses of 1, 2, 4, or  $8 \mu\text{g/kg/day}$  in patients with advanced intraperitoneal malignancy. This study, which also administered GM-CSF intravenously, noted that first dose reaction was seen only after intravenous and not intraperitoneal administration.

We expect fewer and less serious side effects of GM-CSF than described in the above studies because of the intraperitoneal administration route and the low dose that has been chosen.

### **Side effects of the instilled volume**

After the intraperitoneal administration of drugs, a volume of 500 ml will remain as an instillation in the abdominal cavity, which will then be gradually absorbed. In a recent RCT, 500 ml of saline were instilled as an intervention after laparoscopic cholecystectomy to investigate effects on pain, recovery and quality of life. The control group did not receive any fluid instillation. There was no difference in pain, recovery, or quality of life between the two groups. The only significant outcome was increased nausea one hour after surgery in the intervention group. However, there was no difference at the subsequent time points at four hours, one day, and seven days postoperatively. No other adverse effects were reported. Therefore we expect the planned volume of 500 ml to be without side effects for the patients.

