### **The formulation of the drugs**

The formulation of fosfomycin Fomicyt/Infectofos manufactured by Infectopharm is used in this trial and approved for clinical use in Germany. The 4 g of fosfomycin will be diluted in 300 ml of sterile water.

Metronidazole is available in our department as 100 ml *Metronidazol "B. Braun"*, which has a concentration of 5 mg/ml. We will use 200 ml of metronidazole.

The GM-CSF used will be Repomol (molgramostim) from Reponex Pharmaceuticals A/S, which consists of recombinant human GM-CSF expressed in *E. coli* bacteria. We will use a dose of 50 µg in 0.2 ml of solution (water for injections).

The total volume administered intraperitoneally will be 500 ml.

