### **Other drugs during the trial**

The participants can receive any pain medication (paracetamol, ibuprofen, tramadol, or morphine) necessary before or after the surgery. Further, the patients can receive intravenous fluids without restrictions and the necessary thrombosis prophylaxis. In addition, medication necessary for anaesthesia and nausea can be administered without restrictions.

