### **Measurements**

Primary outcome:

- Preoperatively, white blood cell counts at admission (baseline) compared with white blood cell counts 4 hours  $\pm$  30 minutes postoperatively are analysed by Department of Clinical Biochemistry, Herlev Hospital according to their usual standards. The blood samples are destroyed after analysis. A toxic effect defined by a drop below the reference range.

Secondary outcomes:

- Preoperative biochemical markers are analysed at admission (baseline) and 4 hours  $\pm$  30 minutes postoperatively by Department of Clinical Biochemistry, Herlev Hospital according to their usual standards. These include a standard panel of blood samples, which are seen in Supplements, Table 3. The blood samples are destroyed after analysis. This requires a total of 20.5 ml blood.
- Vital signs (pulse, blood pressure, temperature, frequency of respiration, and SAT) are measured perioperatively (baseline, 5 minutes, 10 minutes

and 15 minutes after the trial treatment has been administered) and postoperatively (4 and 12 hours  $\pm$  30 minutes after the trial treatment has been administered).

- Length of stay in hours postoperatively.
- Side effects: evaluated through an objective examination and questions about changes 12 hours  $\pm$  30 minutes and 10 days postoperatively  $\pm$  1 day.
- Adverse events: registered from the surgery until 30 days postoperatively through medical records and contact with the participant by telephone.

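### The protocol expects no side effects from the 500 ml volume, although the trial it cites found more nausea at one hour; its own first scheduled side-effect question comes at 12 hours

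*Protocol*

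**What the plan says.** The Protocol section on side effects of the instilled volume rests on one randomised trial, in which "500 ml of saline were instilled as an intervention after laparoscopic cholecystectomy" and the controls received no fluid. Its result is summarised as "The only significant outcome was increased nausea one hour after surgery in the intervention group", and "there was no difference at the subsequent time points at four hours, one day, and seven days postoperatively". The section then ends: "Therefore we expect the planned volume of 500 ml to be without side effects for the patients".

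The section on the formulation of the drugs describes a different fluid: "The 4 g of fosfomycin will be diluted in 300 ml of sterile water" and "We will use 200 ml of metronidazole", plus 0.2 ml of GM-CSF solution.

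Under Measurements for the main trial, the entry reads "Side effects: evaluated through an objective examination and questions about changes 12 hours" (± 30 minutes), and then again at 10 days. Adverse events are registered separately, from surgery to day 30, through medical records and a telephone contact. Before 12 hours, the main trial schedules vital signs at baseline, 5, 10 and 15 minutes and 4 hours, and a blood sample at 4 hours.

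On antiemetics, the main-trial section on other drugs says: "In addition, medication necessary for anaesthesia and nausea can be administered without restrictions". The corresponding sub-trial section gives similar freedom and adds that these medicines are entered in the CRF. The main-trial section has no such line.

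**The concern.** The closing sentence on volume is presented as following from the cited trial, yet that trial's one positive finding was a side effect of the volume. In a trial whose aim is safety, this misstates the risk.

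The schedule has a related weakness. The protocol's own source places the effect at about one hour and finds no difference at four hours, but patients are first asked about symptoms at 12 hours. Side effects are a named secondary outcome, and the protocol says that, to its authors' knowledge, this combination has not been given before. Table 1 lists nausea as a common side effect of metronidazole and GM-CSF, and vomiting as one of fosfomycin and GM-CSF. The GM-CSF section also describes a first-dose reaction at 60 ± 40 minutes after intravenous dosing, with nausea and vomiting among its symptoms. The protocol reports that this reaction was not seen after intraperitoneal dosing. A schedule with no symptom question in the first hours is poorly placed to confirm that.

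At stake is how complete, and how well timed, the record of early nausea and vomiting will be.

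**Working it through.** **1. The volume figure.** Components from the formulation section: 300 ml + 200 ml + 0.2 ml = 500.2 ml, which agrees with the stated 500 ml. The volume matches the cited trial; the fluid and the operation do not.

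**2. Evidence against conclusion.**

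| Item | Cited trial, as summarised in the protocol | This trial |
|---|---|---|
| Volume | 500 ml | 500 ml |
| Fluid | Saline | 300 ml sterile water with fosfomycin, 200 ml metronidazole solution, 0.2 ml GM-CSF solution |
| Operation | Laparoscopic cholecystectomy | Laparoscopic appendectomy |
| Nausea at 1 h | Significantly more than with no fluid | No symptom question scheduled |
| Nausea at 4 h | No difference | Vital signs and blood sample; no symptom question scheduled |
| Conclusion drawn | – | No side effects expected |

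One significant early effect that was no longer detectable at the next time point supports no lasting side effects. It does not support none. The step from saline to the trial fluid is a further assumption, which the section does not mention.

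**3. Timing.** The 12 h ± 0.5 h window runs from 11.5 to 12.5 h after treatment. I treat hours after surgery and hours after instillation as the same, because the fluid goes in at the end of the operation.

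- Distance from the 1 h point: 11.5 − 1 = 10.5 h to 12.5 − 1 = 11.5 h.
- Distance from the 4 h point: 11.5 − 4 = 7.5 h to 12.5 − 4 = 8.5 h.

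These figures measure how far back a patient must recall. They do not measure lost data.

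**4. Who already has an early contact.** All 14 have the 4 h contact. The sub-trial draws blood at 1 h ± 15 minutes. If the expected eight sub-trial participants all come from the main trial, 14 − 8 = 6 have no scheduled contact between 15 minutes and 4 h. For the same 6, the protocol text does not state that antiemetics are noted in the CRF.

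**5. What 14 patients in one arm can show.** The protocol gives no nausea rates, so the rates in the second item are assumptions.

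- If no nausea were recorded in 14, the exact two-sided 95% upper limit would be 1 − 0.025^(1/14) = 0.232, about 23%. An empty record would not show that there is no effect.
- Suppose there were also 14 untreated controls, and take the normal approximation at two-sided 0.05. Power to detect a 20-point excess would be 0.205 (20% v 40%), 0.184 (30% v 50%) and 0.179 (40% v 60%). With no controls at all, an excess due to volume cannot be estimated, whatever the timing of the question.

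**The case against.** The strongest reply is that early nausea has several routes into the record.

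- Adverse events are registered from surgery onward through medical records.
- The 12 h question looks back over the preceding hours, and patients are also asked about any unfavourable symptom regardless of cause.
- Standard postoperative monitoring continues, with added direct contact with the investigator.
- The discharge score has an item that distinguishes drinking fluids, nausea, and nausea with vomiting.

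This stands, and it limits the point. A reader might infer that early nausea will be missed, or else counted against the drugs because the volume has been declared harmless. The documents support neither. The routes above can capture it, and no section assigns nausea to the drugs by default; it could equally be put down to anaesthesia or surgery. The aim is also the safety of the intraperitoneal administration of the combination, so the 500 ml is part of what is being tested. Nausea counted against the instillation is not wrongly counted.

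These routes do not supply a set time or a uniform question. Recall at 12 hours follows an anaesthetic, charting varies with staff, and the discharge score serves discharge: nausea that had resolved would score as able to drink. No section makes that score a side-effect measure.

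Two further replies are fair. The fluid difference is indirectness, openly visible in the protocol, and nothing in it shows that the vehicle changes nausea. The CRF is a separate document, so the main-trial text's silence on recording antiemetics does not prove that the field is absent.

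**Conclusion.** The conclusion about the volume is wrong as written, because it contradicts the result reported just before it. The source supports no lasting side effects at most, and only indirectly. This rests on the protocol's own summary of the cited trial.

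The schedule is a weakness of moderate to small size. No symptom question is set before 12 h ± 30 min, so transient nausea in the first hours depends on recall over 10.5 to 11.5 h or on charting. It affects all 14 participants, but it concerns a secondary outcome and an effect that was transient in the cited trial; the primary outcome, the white blood cell count, is untouched.

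It would be tempting to say that an earlier question would separate volume effects from drug effects. It would not. In a single arm, nausea at one hour may come from the volume, the drugs, the anaesthetic or the operation. What an earlier question gains is a better-timed and less recall-dependent safety record. That is worth having because it is cheap.

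**What to change.** 1. Reword the end of the section on the instilled volume. Say that transient early nausea was seen with the same volume of saline and may be expected, that no lasting effect was reported, and that the evidence comes from a different fluid and operation.
2. Add a yes/no nausea and vomiting question, covering the time since surgery, at the existing 4 h contact for all 14. Ask it also at the 1 h sub-trial blood sample, for those who have that contact.
3. State that antiemetic use is noted with clock time for all main-trial participants, in line with the sub-trial text on recording such medicines.
4. Report nausea and vomiting by time since instillation, as an effect of the whole intraperitoneal treatment, without claiming to separate volume from drugs.

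The cost is a rewritten sentence or two and a few CRF fields. No new visit is needed, and no dose or clinical rule changes. The downside is slightly more CRF work and probably a higher recorded nausea count, which the report should explain as fuller ascertainment.
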